## Abstract

**Background:**

Tobacco cessation medication adherence is one of the few factors shown to improve smoking cessation rates among methadone-maintained smokers, but interventions to improve adherence to smoking cessation medications have not yet been tested among methadone treatment patients. Methadone clinic-based, directly observed therapy (DOT) programs for HIV and tuberculosis improve adherence and clinical outcomes, but have not been evaluated for smoking cessation. We describe a randomized controlled trial to evaluate whether a methadone clinic-based, directly observed varenicline therapy program increases adherence and tobacco abstinence among opioid-dependent drug users receiving methadone treatment.

**Methods/Design:**

We plan to enroll 100 methadone-maintained smokers and randomize them to directly observed varenicline dispensed with daily methadone doses or treatment as usual (self-administered varenicline) for 12 weeks. Our outcome measures are: 1) pill count adherence and 2) carbon monoxide-verified tobacco abstinence. We will assess differences in adherence and abstinence between the two treatment arms using repeated measures models.

**Discussion:**

This trial will allow for rigorous evaluation of the efficacy of methadone clinic-based, directly observed varenicline for improving adherence and smoking cessation outcomes. This detailed description of trial methodology can serve as a template for the development of future DOT programs and can guide protocols for studies among opioid-dependent smokers receiving methadone treatment.

**Trial Registration:**

clinicaltrials.gov NCT01378858

## Background

Methadone maintenance treatment patients have a disproportionately high prevalence of tobacco use and suffer high rates of tobacco-related disease and mortality [1-6]. Cessation approaches evaluated to date among opioid-dependent smokers, including nicotine replacement therapy, bupropion, or varenicline in combination with behavioral therapy, have not been effective over control conditions [7-11]. Varenicline’s demonstrated efficacy may not be generalizable to methadone-maintained smokers because of poor adherence, which is highly prevalent among drug users [11-15]. Though adherence to smoking cessation treatment is a critical determinant of successful cessation [16-23] and adherence is one of the few factors shown to increase cessation among methadone-maintained smokers [12,24,25], interventions to improve adherence to smoking cessation pharmacotherapy have not yet been tested in this group.

Administration of directly observed therapy (DOT) for tuberculosis (TB) and HIV regimens at opioid agonist treatment programs has been shown to improve adherence and clinical outcomes among methadone maintenance patients [26-30]. Methadone maintenance programs provide an ideal setting for DOT administration. Regulatory requirements mandate that patients attend methadone programs up to 6 times weekly, minimizing barriers to medication adherence, and providing a platform for treatment of other diseases. Because of the limited treatment course and low pill burden of smoking cessation treatment, it may be even more feasible to implement DOT for smoking cessation treatment than for TB or HIV treatment. To our knowledge, no studies to date have evaluated DOT for smoking cessation.

We thus designed a randomized trial of modified, directly observed versus self-administered varenicline therapy in methadone clinics to evaluate the efficacy of modified DOT (mDOT) for improving varenicline adherence and smoking cessation among methadone-maintained smokers, and to test whether drug use and psychiatric symptoms moderate the effects of mDOT on adherence.

## Methods/Design

This is a randomized pilot trial of modified directly observed versus self-administered varenicline therapy among 100 methadone-maintained smokers. We will evaluate the efficacy of mDOT varenicline for promoting smoking cessation and medication adherence with research visits at baseline and at 1, 2, 3, 6, 9, 12, and 24 weeks. We will also evaluate the moderating effects of illicit drug use and psychiatric symptoms on mDOT adherence effects.

### Study setting

Participants will be recruited from the Einstein Division of Substance Abuse (DoSA) methadone clinics, which offer integrated substance abuse and medical treatment to 3200 patients in three clinical sites in the Bronx, New York. Established in 1968, DoSA is a clinical, research, and educational division of the Einstein Department of Psychiatry. Each clinic offers comprehensive medical services, integrating general and HIV-related medical and gynecologic services with co-located substance abuse treatment.

### Participants

Our goal is to enroll subjects representative of methadone-maintained smokers, while considering varenicline precautions. Eligible persons are: 18 years or older; smoking 5 or more cigarettes per day; interested in quitting smoking with a plan to quit in ≤ 6 months (ladder of change score 6–8); enrolled in methadone treatment for at least 3 months, receiving methadone in the clinic 3, 4, 5, or 6 times per week, without three or more clinic absences in the prior 2 weeks; English-speaking; able to provide informed consent; not pregnant, breastfeeding, or trying to conceive; and have not taken varenicline in the past 30 days. Unstable liver, cardiac, pulmonary, renal, or infectious diseases are exclusionary. Psychiatric exclusion criteria include current major depressive or manic episode, current psychotic disorder, past-year suicide attempt or psychiatric hospitalization, or current suicidal ideation with plan or intent.

Subjects will be recruited by research assistants in methadone clinic waiting areas, as well as by word-of-mouth, posted fliers, and clinic counseling and medical staff referral. All subjects will sign written informed consent. We will conduct a brief screening interview, then abstract laboratory and treatment data from clinic charts to further assess eligibility. Eligibility will be confirmed only after the study physician completes a clinical and structured psychiatric interview using the Mini-International Neuropsychiatric Interview 6.0.0 (M.I.N.I.) and Columbia Suicide Severity Rating Scale, and conducts a physical examination and urine pregnancy test (if applicable). Interviews will be completed in private offices in the methadone clinics.

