### Interventions

Subjects will receive varenicline for 12 weeks, using standard dosing: 0.5 mg once daily for 3 days, then 0.5 mg twice daily for 4 days, followed by 1 mg twice daily for 11 weeks. Subjects will be randomly assigned to receive varenicline via: 1) treatment as usual (TAU) or 2) modified directly observed therapy (mDOT). Most subjects will have public insurance that should cover the cost of varenicline; for those who do not, varenicline will be purchased from a local pharmacy using research funds.

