### Visit schedule and measures

Research visits will be scheduled at baseline and at weeks 1, 2, 3, 6, 9, 12, and 24 (Table 1). We will collect survey data using Audio Computer-Assisted Self-Interview (ACASI), which has been shown to improve reporting of stigmatized behaviors. Subjects will be reimbursed up to $110 for completing all research assessments. Retention will be enhanced by flagging subjects for research visits at the methadone clinic reception desk, tracking contact information of subjects and their close contacts at each study visit, reimbursement for completion of assessments, and on-site data collection at subjects’ clinics.

**Table 1 T1:** Timing of study measures

	**Baseline/Start Rx**						**End of treatment**	
**Week**		1	2	3	6	9	12	24

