### Adherence measures

Our primary outcome is adherence (as a continuous measure) by pill count. Pill counts are an objective measure that have been shown to correlate with electronic monitors [32]. The amount of medication taken during the 12-week treatment course will be expressed as a percentage of the target dose. These are established measures used in other DOT trials in our setting [29,33]. Self-report is the most practical adherence measure for clinical use, and it has been shown to correlate with clinically relevant outcomes in several studies [34-37]. Though self-report is subject to recall and reporting bias and may overestimate adherence [32,36,38,39], we will use self-report as a second measure of adherence because it is easy to administer and is generalizable. Because electronic monitors (using medication event monitoring systems [MEMs]) cannot be used in the mDOT arm, we have chosen not to use MEMs.

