### Tobacco use measures

Our primary tobacco use outcome is biochemically validated 7-day point prevalence abstinence at each follow-up visit, with abstinence defined as including both self-reported smoking abstinence and carbon monoxide (CO) < 8 p.p.m. (Micro Smokerlyzer®, Bedfont Scientific) [40]. Self-reported tobacco abstinence will be measured at all visits by asking participants, “Have you smoked at least part of a cigarette in the past 7 days, even a puff?” Our secondary tobacco outcome measures include: 1) number of cigarettes smoked per day; 2) Fagerström Test for Nicotine Dependence score; 3) quit attempts lasting ≥ 24 hours; and 4) durability, measured by CO-verified tobacco abstinence at week 24.

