### Tobacco use

We hypothesize subjects in the mDOT arm will have greater CO-verified, 7-day point prevalence abstinence throughout the intervention period; reductions in cigarettes/day and Fagerström Test for Nicotine Dependence scores; and ≥ 24-hour quit attempts compared to subjects receiving self-administered varenicline. We will compare the proportion of participants who achieve CO-verified tobacco abstinence at all follow-up timepoints in the two study arms using mixed-effects models. In addition, we will compare secondary tobacco use outcomes between study arms using chi-square or Wilcoxon rank sum tests, and explore differences in CO-verified abstinence at 24 weeks using Fisher exact tests. All analyses will use an intent-to-treat approach. In addition, we will apply mixed effects models to test the significance of varenicline adherence on smoking cessation across the post-baseline assessment time points.

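### Entry accepts a quit plan up to 6 months ahead, beyond the 12-week treatment, which may dilute on-treatment abstinence; the ladder score should be a prespecified covariate

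*Protocol article*

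**What the plan says.** The Participants section of the protocol article sets the motivation criterion as "interested in quitting smoking with a plan to quit in ≤ 6 months" (ladder score 6–8), and gives enrolment of a representative group of methadone-maintained smokers as its goal.

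The timeline is shorter than that window. Under Interventions, "Subjects will receive varenicline for 12 weeks". Table 1 heads its first column "Baseline/Start Rx" and marks week 12 as the end of treatment. Under Visit schedule and measures, "Research visits will be scheduled at baseline and at weeks 1, 2, 3, 6, 9, 12, and 24". Table 1 lists smoking endpoints at weeks 3, 6, 9, 12 and 24.

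The outcomes are ranked. Under Adherence measures, "Our primary outcome is adherence (as a continuous measure) by pill count". Under Tobacco use measures, "Our primary tobacco use outcome is biochemically validated 7-day point prevalence abstinence at each follow-up visit"; abstinence at week 24 is a secondary measure there, labelled as durability. The hypothesis in the Tobacco use analysis section is that mDOT gives "greater CO-verified, 7-day point prevalence abstinence throughout the intervention period". The same section plans a model of the effect of adherence on cessation.

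The ladder score is named only in the entry criterion. Randomization is stratified by site and HIV status. The adherence model takes baseline variables that turn out unequal between arms, plus psychiatric symptoms and substance abuse. The listed moderators are drug use, alcohol use and psychiatric variables.

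**The concern.** The trial's reasoning runs from mDOT to better adherence, and from better adherence to abstinence. The second step needs people who try to quit while they have the drug. A smoker who plans to quit in month 4, 5 or 6 meets the criterion. If that plan is kept, the smoker is non-abstinent at weeks 3, 6, 9 and 12 however well the pills are taken.

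Three things are at stake:

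- **Power for abstinence.** Participants who cannot show an on-treatment difference shrink the average difference. A null result would then be hard to read.
- **The adherence–cessation model.** Adherence is not randomized. Intention to quit soon may drive both pill-taking and abstinence, so leaving it out may confound this association.
- **The week-24 label.** A first quit after treatment has ended would count as abstinence at week 24 and be read as durability, although there was no on-treatment quit to last.

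**Working it through.** **Calendar.** Six months is 6 × 365.25 / 12 / 7 = 26.1 weeks, taken as 26. The window runs 26 − 12 = 14 weeks past the end of treatment (14/26 = 54% of the window) and 26 − 24 = 2 weeks past the last visit (2/26 = 8%). These are shares of the window, not of participants.

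**The plan's own figure.** Sample size and power considerations gives 22% versus 44%, two-sided α = 0.05, and 29, 33 and 38 per group for ICC 0.1, 0.2 and 0.3. Neither the power nor the number of repeated measures m is stated. The single-time formula is

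n = [z₀.₉₇₅ √(2p̄(1−p̄)) + z_power √(p₁(1−p₁) + p₂(1−p₂))]² / (p₂−p₁)².

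With p̄ = 0.33 and 80% power, n = (1.960 × 0.6650 + 0.8416 × 0.6465)² / 0.0484 = 70.5. Multiplying by (1 + (m−1)·ICC)/m with m = 3:

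- ICC 0.1: 70.5 × 0.400 = 28.2, rounded up to 29
- ICC 0.2: 70.5 × 0.467 = 32.9, rounded up to 33
- ICC 0.3: 70.5 × 0.533 = 37.6, rounded up to 38

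All three match. No other m from 2 to 7 at 80% power matches all three, nor does any at 90%, so 80% power and m = 3 are inferred. With 25% attrition, 76/0.75 gives 102, close to the planned 100. Completers per arm are 50 × 0.75 = 37.5, so there is almost no slack at ICC 0.3.

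**Illustration of dilution.** Let f be the share who plan to quit after week 12. Assume that they have no abstinence through week 12 in either arm and that 22% and 44% hold for the rest. Each rate is multiplied by (1 − f). The rate ratio stays at 2 and the difference becomes 22(1 − f) points. N and power use the same formula with m = 3.

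| f | TAU vs mDOT | Difference (points) | N per group at 80% power, ICC 0.1/0.2/0.3 | Power with 37.5 per arm, ICC 0.1/0.2/0.3 | Total N after 25% attrition, ICC 0.3 |
|---|---|---|---|---|---|
| 0 | 22% vs 44% | 22 | 29/33/38 | 90/85/80% | 102 |
| 10% | 19.8% vs 39.6% | 19.8 | 33/39/44 | 85/79/73% | 118 |
| 25% | 16.5% vs 33% | 16.5 | 43/50/57 | 75/68/62% | 152 |
| 50% | 11% vs 22% | 11 | 72/83/95 | 53/47/42% | 254 |

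The values of f are assumptions. The article gives no distribution of planned quit dates or ladder scores.

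**Route for the ladder score.** Comparing the Participants, Randomization, Varenicline adherence, Tobacco use and Moderating effects sections shows one possible route into a model: the rule that brings in baseline variables found unequal between arms. That rule depends on the data and is stated only for the adherence model.

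**The case against.** The strongest reply is that an upper limit on intention is not a quit date. The criterion also covers someone who plans to quit tomorrow. Everyone enrolled starts a cessation drug at baseline and has a physician counseling session (Counseling and medication education), which may bring quits forward. A target quit date may be set in the full protocol that the article condenses, so its absence here is no error. All of this stands, and it is why the size cannot be fixed.

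A wide window also serves the stated aim of a representative sample. That stands too and argues against narrowing entry. The trial is a pilot, and its limitations paragraph already concedes limited ability to compare abstinence for smaller effects. The 22% TAU rate was also already discounted for methadone patients, so further dilution may partly count the same thing twice.

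A reader might infer more than the documents support:

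- **That late intenders are failures throughout.** They are non-abstinent at weeks 3 to 12 if they keep to the plan, but a quit between weeks 12 and 24 can count at week 24.
- **That the arm comparison is biased.** Randomization makes the share similar in both arms.
- **That the primary outcome is damaged.** Pill-count adherence does not depend on a quit date, and nothing in the article shows that late intenders take fewer pills.
- **That 54% of participants are affected.** That figure is calendar arithmetic.
- **That a ladder score of 6 marks the late intenders and 7 or 8 the rest.** The article does not say what the scores mean.

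What remains is that the window exceeds the treatment period and that no described analysis prespecifies the score.

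**Conclusion.** The point holds in a limited form. The quit-intention window is about 14 weeks longer than the treatment over which the abstinence hypothesis is stated. Participants who plan to quit after week 12 may dilute the on-treatment abstinence difference. This lowers both arms' rates in the same proportion and costs power, without biasing the randomized comparison. The amount cannot be derived from the article; the table shows only what would follow if late intenders had no on-treatment abstinence.

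Two further consequences need no figure for the share: quit intention may confound the non-randomized adherence–cessation model, and first quits after treatment would blur the reading of week-24 abstinence as durability. The matter is an inexpensive improvement to the analysis, and the entry criterion is not an error.

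**What to change.** Keep the entry criterion. Prespecify the baseline ladder score as an ordered covariate, without a 6 versus 7–8 split, in three models: abstinence, pill-count adherence, and adherence on cessation. Do not leave its inclusion to the baseline-imbalance rule. Report abstinence at each visit by ladder score and arm, descriptively. At week 24, this also helps the reader to judge how far abstinence can be called durability.

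The score is already obtained for eligibility, so no new data are needed. Adjustment does not restore a difference that was diluted; it makes the result easier to interpret and may recover some precision. The downside is one more parameter in a binary model that may have few events. At the 10.5% and 4% abstinence reported in the limitations paragraph for two varenicline trials, 50 participants per arm would give about 5 (50 × 0.105) or 2 (50 × 0.04) abstainers in an arm.

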**Figure 1 F1:**
[figure not shown]
**Example mDOT varenicline pill trays. A**. Methadone clinic visits 3 days per week. **B**. Methadone clinic visits 6 days per week. This figure illustrates mDOT varenicline pill box labels indicating observed and take-home varenicline doses, according to subjects’ methadone clinic schedule.

We describe the intervention as ‘modified directly observed therapy’ because varenicline ingestion will be observed at the methadone window 3–6 days per week based on the subject’s methadone clinic schedule. Furthermore, varenicline is a twice-daily medication, and only one of two daily varenicline doses can be observed. For example, if a subject receives methadone at his/her program Monday through Saturday and a take-home dose of methadone on Sunday, s/he would receive observed varenicline at the same time s/he receives methadone Monday through Saturday (for a total of six observed doses), and would get pill boxes for evening and Sunday varenicline doses (eight unobserved doses weekly). Subjects will be instructed to return the pill boxes for unobserved doses at their next clinic visit, whether or not they have taken the pills.

To minimize nursing burden, trays of pill boxes will be prepared by research assistants, indicating varenicline dosing and dates of administration, and color-coded labels will indicate whether the dose is directly observed or self-administered (for days off and evenings). Each tray will hold seven removable pill boxes, with compartments for morning and evening varenicline doses. The study physician will call in varenicline prescriptions to a single, designated, community pharmacy that delivers medications to the DoSA central pharmacy. Empty, labeled trays also will be delivered to the central DoSA pharmacist, who will fill pill boxes with varenicline for each subject. Filled trays will be delivered from the central pharmacy to the methadone clinics every 2 weeks, along with scheduled methadone deliveries.

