### Randomization

Subjects will be randomized a 1:1 ratio in variable size blocks of 2–8 via central, computer-generated randomization. Randomization will be stratified by clinical site and HIV status. We will randomize in blocks to ensure comparison groups of approximately equal size. To ensure concealment of allocation, a centrally-located data manager will generate the allocation sequence and store the sequence in a password-protected file. After the study physician confirms a subject’s eligibility, she will call the data manager, who will assign the subject to a treatment group. Since the intervention is not blinded, we will vary block size to prevent anticipation of treatment arm assignment.

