### Moderating effects of drug use and psychiatric symptoms

We hypothesize that ongoing drug use and psychiatric symptoms will negatively moderate adherence effects. The dependent variable will be varenicline adherence. Potential moderating variables include cocaine, heroin, benzodiazepine, or marijuana use (defined as a binary variable based on either self-reported use or positive urine toxicology result); hazardous alcohol use (defined as AUDIT score ≥ 8 for men and ≥ 4 for women); incident major depressive, manic, or psychotic episodes; suicidal ideation with plan or intent; and symptoms of psychologic distress (BSI Global Severity Index T score ≥ 63). We will test moderators using a treatment group x moderating variable interaction term, and set an alpha significance level of 0.15 for interaction analyses.

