### Sample size and power considerations

Among methadone-maintained smokers receiving a nicotine patch in a clinical trial, overall adherence over 90 days was 44.1 percent [12]. Assuming a 13-percent difference in adherence between the DOT and TAU groups as seen in weeks 2–12 of a methadone clinic-based antiretroviral DOT trial [30], the hypothesized adherence effect would be 57 percent in the mDOT arm and 44 percent in the TAU arm. We estimate sample sizes N per group required to detect this effect at a two-sided α = 0.05 as N per group = 11, 14, and 17 for intraclass correlation (ICC) = 0.1, 0.2, and 0.3, respectively.

Given that the efficacy of NRT and bupropion in methadone maintenance patients has been half of that observed in clinical trials of these medications in the general population [7,8,15], we estimate that abstinence rates at 12 weeks in the TAU varenicline arm would be 22 percent. We estimate that increased adherence would double the odds of cessation [13,17,18,46], and thus the abstinence rates at 12 weeks in the DOT arm would be 44 percent. We estimate sample sizes required to detect the hypothesized intervention effect (22% and 44% on a binary scale) at a two-sided alpha = 0.05 as N per group = 29, 33, 38 for within-subject ICC = 0.1, 0.2, and 0.3, respectively. Estimating an approximately 25 percent attrition rate at 12 weeks, we plan to recruit 100 participants.

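### Clinic visits per week at entry set how many mDOT doses can be observed (21% to 43%), yet visit schedule is neither a prespecified covariate nor a listed moderator

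*Protocol article*

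**What the plan says.** Under Participants, eligibility covers patients "receiving methadone in the clinic 3, 4, 5, or 6 times per week, without three or more clinic absences in the prior 2 weeks". The text below Figure 1, in the description of the DOT intervention, explains that observation follows each patient's methadone schedule and that "only one of two daily varenicline doses can be observed". Its worked example, a patient attending six days a week, has six observed and eight unobserved doses.

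Under Randomization: "Randomization will be stratified by clinical site and HIV status". Under Varenicline adherence, the mixed model adds psychiatric symptoms, substance abuse and any variable found unequal between the arms at baseline. Under Moderating effects, the hypothesis is: "We hypothesize that ongoing drug use and psychiatric symptoms will negatively moderate adherence effects". The candidates listed there are drug use, hazardous alcohol use, psychiatric episodes, suicidal ideation and psychological distress, each tested by an interaction with treatment group at alpha 0.15. Visit schedule is not among them.

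The sample size section plans one effect for the whole mDOT arm: "Assuming a 13-percent difference in adherence between the DOT and TAU groups", that is, 57% against 44%.

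**The concern.** Observed dosing is the core of the intervention, and how much of it a patient can receive is fixed by a baseline characteristic that the eligibility criterion already records. Patients at the two ends of the permitted range differ by a factor of two in the observation they can be given, yet the plan produces a single averaged effect and tests only other moderators.

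The rule on baseline imbalance does not fill the gap. It depends on what the data happen to show, and it yields an adjustment term rather than an interaction.

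What is at stake is interpretation. The article calls the trial a pilot, says it should inform effect sizes for later studies, and offers its methods as a template for future DOT programs. If the average effect is null or small, a reader will want to know whether observed dosing failed or whether too few doses were observed. As written, the plan has no analysis directed at that question.

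**Working it through.** **Inputs from the article.** Visits per week v = 3, 4, 5 or 6 (Participants). One observable dose per visit (text under Figure 1). 14 doses in a full-dose week, from the article's own example: 6 + 8 = 14. Control adherence 44% and mDOT adherence 57%, a difference of 13 points (Sample size).

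**Observable share = v/14.**
- 3 visits: 3/14 = 21.4%
- 4 visits: 4/14 = 28.6%
- 5 visits: 5/14 = 35.7%
- 6 visits: 6/14 = 42.9%, which matches the article's example

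Counting the first week at its lower number of doses gives 3 + 8 + 154 = 165 doses over the course, and the range becomes 36/165 = 21.8% to 72/165 = 43.6%. The picture does not change.

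**Largest gain from observation alone.** Assume that every observed dose is taken and that unobserved doses stay at the control level of 44%. The article states neither. Then gain = (v/14) × (100 − 44):
- 3 visits: 12 points (adherence 56%)
- 4 visits: 16 points (60%)
- 5 visits: 20 points (64%)
- 6 visits: 24 points (68%)

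Each extra weekly visit is worth 56/14 = 4 points. Only the 3-visit ceiling is below 13, and by 1 point. Unobserved adherence of (57 − 21.4)/(100 − 21.4) = 45.3% instead of 44% closes that gap. The 3-visit ceiling also moves with the assumed control adherence: 13.9 points at 35%, 10.7 at 50%, 8.6 at 60%.

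**Does this threaten the main comparison?** The article quotes 11, 14 and 17 per group for ICC 0.1, 0.2 and 0.3 without a power or a standard deviation, so these can only be back-solved. With 6 measurements, 80% power and an SD of 20.8 points (assumed), 2 × (20.8 × 2.80/13)² × (1 + 5 × ICC)/6 gives 10.05, 13.40 and 16.74, which round up to 11, 14 and 17. About 37 per arm remain after 25% attrition from 100. At ICC 0.3 the standard error of the arm difference is 20.8 × √(2.5/6) × √(2/37) = 3.12 points. Even if every patient were on 3 visits and the true effect were 12 points, power would be about 97%. With an assumed SD of 30 it would be about 76%.

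**What would the missing interaction test deliver?** Suppose, since the article gives no mix, that patients are spread evenly over the four schedules. The SD of visits is then √1.25 = 1.118, and the standard error of the difference in slopes is 3.12/1.118 = 2.79 points per visit. For a true 4 points per visit, 4/2.79 = 1.43 against a critical value of 1.44 at alpha 0.15, so power is about 50%. With SD 30 it is about 34%. The term is informative but not decisive.

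**The case against.** The variation is deliberate and disclosed. The article aims to enrol patients representative of methadone-maintained smokers and calls the intervention modified because observation depends on the schedule; an average over real schedules is a legitimate target for a pilot. Leaving a factor out of the strata does not bias a randomised comparison, and the imbalance rule could bring schedule into the model. Nurses record each day whether doses were dispensed, refused or missed, so observed dosing will be known for each mDOT patient. The article also concedes that its sample may not settle moderator questions. All of this stands. It limits the point to interpretation, but it does not supply a planned test of schedule by arm. The nurse records describe doses after randomisation in one arm only, whereas baseline schedule is available in both.

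A reader might go further and infer that patients on 3 visits can barely reach the planned effect. The documents do not support that. It requires take-home adherence to stay at exactly 44%, although the mDOT arm also has labelled pill boxes that must be returned and scripted nurse contact. It also sets one subgroup's ceiling against a whole-arm average, with the share of 3-visit patients unknown.

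Nor does the article show that HIV status is the wrong stratum: a stratification factor needs no hypothesis of its own, and exchanging it is a trade-off. The absence criterion, "without three or more clinic absences in the prior 2 weeks", is a fixed count and so means a different attendance rate on each schedule, but it applies before randomisation and equally to both arms.

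**Conclusion.** The point holds as a gap in the planned analyses, not as an error or a source of bias. The observable share of doses differs twofold by a baseline variable (21% to 43%). That figure rests only on the eligibility range and the one-dose-per-visit limit, both stated in the article. Neither the adherence model nor the moderator list provides for testing whether the effect varies with it.

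The 12 to 24 point ceilings illustrate why it could matter and depend on the two assumptions named in the check. They do not show that the planned 13 points is out of reach for the trial or for any schedule group. The article-based margin on the adherence outcome is wide unless the SD is well above the back-solved value. The consequence is confined to how a null or small average effect, or an effect size carried into a later study, can be read.

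**What to change.** In the Varenicline adherence section, name scheduled clinic visits per week at entry as a covariate whether or not the arms differ on it. In the moderator section, add schedule by arm to the list, with visits per week entered as a number, labelled exploratory and reported as an estimate with its interval.

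The data are already collected at screening in both arms, and the interaction framework exists, so the cost is one covariate and one term. The drawback is one more low-powered test, subject to the caution about moderators that the article's limitations paragraph already gives. The stratification factors and the eligibility criteria can stay as they are.
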